## Abstract

Background

Depression is a global disease with high prevalence, recurrence, and disability rates. Currently, antidepressant chemical drug therapeutic regimens are the mainstay, but they have low recovery rates, and a significant portion of patients develop refractory depression. Consequently, traditional Chinese medicine (TCM) has emerged as a crucial alternative, with various studies investigating its potential in both standalone and adjunctive treatments for depression. Thus, this study aims to explore the efficacy and safety of an integrated TCM and Western medicine antidepressant therapeutic regimen, i.e., the combination of Shuganjieyu capsules and fluoxetine, in patients with moderate to severe depression (17-item Hamilton Rating Scale for Depression (HAMD-17) score ≥ 18 and Item 13 score ≥ 2) in the short- and long-term (8 weeks and 16 weeks, respectively).

Methods

The study will be divided into a basic study period (0-8 weeks) and an extended study period (9-24 weeks). The basic study period will employ a multicentre, randomized, double-blind, placebo-parallel controlled study, in which patients with moderate to severe depression will be selected and randomly assigned at a 1:1 ratio, with 80 patients in each group. The extended study period will utilize a multicentre, open-label observational study. During the basic study period, the experimental group will receive oral fluoxetine (20 mg/dose, once daily) and Shuganjieyu capsules (two capsules/dose, twice daily, morning and evening), whereas the control group will receive fluoxetine (20 mg/dose, once daily) and a Shuganjieyu capsule simulant (two capsules/dose, twice daily, morning and evening). The dosing regimen for the extended study period will be formulated on the basis of the condition of the subjects after 8 weeks of the basic study period. The primary efficacy endpoint will be the change in the HAMD-17, and the secondary efficacy endpoint will include the change in the Hamilton Anxiety Rating Scale (HAMA), Clinical Global Impression (CGI), Patient Health Questionnaire-15 (PHQ-15), Pittsburgh Sleep Quality Index (PSQI), Dimensional Anhedonia Rating Scale (DARS), Temporal Experience of Pleasure Scale (TEPS), and Quality of Life Enjoyment and Satisfaction Questionnaire-Short Form (Q-LES-Q-SF).

Discussion

This study aims to evaluate the efficacy and safety of the combination of TCM and Western medicine in the acute treatment of moderate to severe depression. Additionally, it seeks to explore the long-term efficacy (in terms of improving residual symptoms and preventing relapse) and safety of this combination therapy. The ultimate goal will be to develop an optimized treatment regimen for depression that combines traditional Chinese medicine and Western medicine, thereby offering more options for the clinical management of moderate to severe depression.

## Introduction

Depression is a highly disabling disorder worldwide that is characterized mainly by a significant and persistent depressed mood, manifested by symptoms such as low mood, diminished interest, and impaired cognitive functioning [1, 2]. Some patients may also present with somatization symptoms, such as insomnia or drowsiness, decreased appetite, fatigue, and hyposexuality. In severe cases, patients may engage in self-injurious or even suicidal behaviours [3], making it the third leading cause of death and disability [1]. According to the World Health Statistics 2023, it is estimated that 3.8% of the world’s population suffers from depression, including 5% of adults and 5.7% of elderly individuals aged 60 years and above [4]. Moreover, more than 10% of pregnant and postpartum women worldwide are affected by depression [5]. Research also predicts that, by 2030, depression may become the most prevalent disease worldwide [1].

Common treatments for depression currently include pharmacological and nonpharmacological therapies [6-10]. In pharmacological therapy, selective serotonin reuptake inhibitors (SSRIs) are among the most commonly used antidepressant drugs in clinical practice [11], and their mechanism of action primarily involves selectively inhibiting the reuptake of serotonin, thereby exerting antidepressant effects. The Sequenced Treatment Alternatives to Relieve Depression (STAR*D) study has shown that, after acute-phase treatment, there are differences in remission rates among different treatment regimens for patients with depression [12, 13]. The remission rate of the first-stage SSRI, citalopram, is only 36.8%. This study has revealed that 90% of patients with depression who responded to acute-phase treatment still present at least one residual symptom, and the most common residual symptoms include sleep disturbances and appetite/weight disturbances. Several studies have explored other augmentative treatment strategies, such as anti-inflammatory drugs and traditional Chinese medicine (TCM) therapy.

According to TCM, depression belongs to the category of “depression syndrome”, and its main clinical manifestations include depressed mood, emotional restlessness, fullness and stuffiness in the chest and subcostal regions, or ease of anger and crying [14]. TCM treatment emphasizes holistic regulation of the body and mind, achieving personalized treatment plans through multiple approaches, targets, and levels [15]. Integrative treatment combining TCM and Western medicine during the acute phase of depression can shorten the time for medication to take effect, rapidly relieve symptoms, synergistically enhance efficacy, and reduce the adverse effects of antidepressant chemical drugs. In the consolidation and maintenance phases, it can further stabilize symptoms, improve residual symptoms, prevent relapse, and prevent recurrence through holistic regulation [14].

Shuganjieyu capsule is the first traditional Chinese medicine approved by the National Medical Products Administration (NMPA) for the treatment of mild to moderate depression [16], and its main ingredients are extracts of *Hypericum perforatum *(HP) and *Eleutherococcus senticosus *(ES), which are known to effectively soothe the liver, relieve depression, strengthen the spleen, and calm the mind. Pharmacokinetic studies have shown that, when extracts of HP and ES are used in combination, they may synergistically exert antidepressant effects by increasing the plasma concentration of hypericin and shortening the time to reach the concentration of eleutheroside E [17]. The antidepressant mechanism of Shuganjieyu capsule has not been fully elucidated, but current research suggests that it may involve multi-target and multi-pathway regulatory effects. These include modulating the levels of monoamine neurotransmitters in the brain (such as serotonin, norepinephrine, and dopamine), inhibiting the release of inflammatory factors, and enhancing neuroplasticity, thereby exerting its antidepressant effects [18]. Previous studies have preliminarily observed the efficacy of combining Shuganjieyu capsules with antidepressant chemical drugs during the acute phase of depression. The results have indicated that the combination of antidepressant chemical drugs with Shuganjieyu capsules has a synergistic effect, especially on symptoms of depression, anxiety, and insomnia, compared with the antidepressant chemical drug monotherapy group [16, 19, 20]. However, research on the long-term efficacy and safety of their combined use remains limited. Given that depression is a chronic progressive disease, clarifying the long-term effectiveness and safety of integrative treatment combining Chinese and Western medicine will be highly important for clinical practice.

This study aims to combine the concept of whole-course management of depression and establish a basic study period (short-term) and an extended study period (long-term) in the project protocol. Through multidimensional scale assessment, this study will further explore the efficacy and safety of combining Shuganjieyu capsules with antidepressant chemical drugs for both short-term and long-term treatment of depression. Additionally, patient satisfaction with the treatment will be evaluated. The goal is to offer more suitable long-term treatment options for individuals with depression and enhance their overall quality of life.

## Materials and methods

Study design

This study will primarily aim to observe the therapeutic efficacy and safety of an integrated traditional Chinese medicine and Western medicine treatment regimen for depression. The study design will include a basic study period (randomized controlled trial (RCT), 8 weeks) and an extended study period (observational study, 16 weeks). The experimental group will be treated with Shuganjieyu capsules combined with fluoxetine for 24 weeks. In the control group, the medication regimen will be fluoxetine + placebo in the basic study period, and may contain Shuganjieyu capsules + fluoxetine (if 17-item Hamilton Rating Scale for Depression (HAMD-17) score reduction rate less than 50% on the end of week 8) or fluoxetine alone (if HAMD-17 score reduction rate more than 50% on the end of week 8) in the extended study period, so that the purpose of this study design will be to observe whether the early combination of Shuganjieyu capsules with fluoxetine as the basic treatment is more effective compared to fluoxetine alone in the depression patients with poor early efficacy.

The trial will consist of two phases: the basic study period and the extended study period. The overview of the study is shown in Fig. 1.

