**Figure 1 FIG1:**
[figure not shown]
Flowchart of the study HAMD-17: 17-item Hamilton Rating Scale for Depression

Basic Study Period (Weeks 0-8)

A multicentre, randomized, double-blind, placebo-controlled parallel design will be employed. During the basic study period, a stratified and block randomization method will be used. All participants will be randomly assigned at a 1:1 ratio to either the experimental group (Shuganjieyu capsules combined with fluoxetine) or the control group (Shuganjieyu capsule simulant combined with fluoxetine). The evaluation during the basic study period will be conducted via double-blind and single-simulation techniques; i.e., both the investigator and the participants will be required to remain “blinded” during the grouping and evaluation. Additionally, the preparation of the placebo used in the control group will ensure that it matches the experimental drug in sensory aspects (such as dosage form, shape, colour, texture, and odour). The placebo will not contain the active ingredients of the experimental drug. This design will minimize subjective errors and ensure the objectivity and reliability of the trial results.

Extended Study Period (Weeks 9-24)

A multicentre, open-label observational study will be conducted. After completing the 8-week treatment period in the basic study period, the investigator will adjust the dosing regimen according to the condition of the participants, either to continue maintaining the treatment regimen of the basic study period in the experimental/control group or to adjust the dosing regimen for the experimental group. The design of the extended study period aims to align with clinical practice.

Sample Size Calculation and Randomization and Blinding Methods

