During the basic study, the experimental group will receive oral fluoxetine (20 mg/dose, once daily) with Shuganjieyu capsules (two capsules/dose, twice daily, morning and evening). The control group will receive fluoxetine (20 mg/dose, once daily) with Shuganjieyu capsule simulant (two capsules/dose, twice daily, morning and evening). If the HAMD-17 total score reduction rate is less than 20% at the end of the second week, the dosage of Shuganjieyu capsule or simulant will be adjusted to four capsules/dose, twice daily, in the morning and in the evening.

After completing the 8-week basic study period and entering case report form (CRF) data, the investigators at each centre will unblind the drug codes corresponding to individual participants. On the basis of the participants’ condition after 8 weeks of the basic study period, an extended study period medication plan was formulated. For participants who enter the extended study period, if their HAMD-17 total score reduction rate is less than 50%, the fluoxetine dosage will be adjusted to 40 mg/dose once daily for the experimental group. For the control group, Shuganjieyu capsules (two capsules/dose, twice daily, morning and evening) will be added first, and further adjustments to the fluoxetine dosage (40 mg/dose, once daily) will be considered on the basis of changes in the participant’s condition. Participants will be prohibited from concurrently using other antidepressant medications during both the basic and extended study periods. During the basic study period, the use of other auxiliary treatments for depression will be prohibited, such as psychotherapeutic intervention and rehabilitation therapy, modified electroconvulsive therapy, transcranial magnetic stimulation, vagus nerve stimulation, deep brain stimulation, and other physical therapies. During the extended study period, the use of other auxiliary treatments for depression will be prohibited, including modified electroconvulsive therapy, transcranial magnetic stimulation, vagus nerve stimulation, and deep brain stimulation, but psychological interventions will be permitted.

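### The purpose given for the two-period design, early combination versus fluoxetine alone in poor early responders, has no planned comparator after week 8

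*Protocol article*

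**What the plan says.** Study design (Materials and methods) gives one purpose for joining an 8-week randomised period to a 16-week extension: to observe whether early combination is "more effective compared to fluoxetine alone in the depression patients with poor early efficacy". The same sentence sets the control regimen for the extension. It "may contain Shuganjieyu capsules + fluoxetine (if 17-item Hamilton Rating Scale for Depression (HAMD-17) score reduction rate less than 50" per cent at the end of week 8), or it is "fluoxetine alone (if HAMD-17 score reduction rate more than 50% on the end of week 8").

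Dosage Regimen sets out the week-8 step for participants with less than 50% reduction. In one arm, "the fluoxetine dosage will be adjusted to 40 mg/dose once daily for the experimental group". In the other, "For the control group, Shuganjieyu capsules (two capsules/dose, twice daily, morning and evening) will be added first", and a fluoxetine change is considered later, depending on the participant's condition.

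Extended Study Period (Weeks 9-24) describes the step differently. The investigator either keeps the basic-period regimen in the experimental or control group, "or to adjust the dosing regimen for the experimental group"; no adjustment of the control group is mentioned. On design it says: "A multicentre, open-label observational study will be conducted". Individual treatment codes are opened after the 8-week visit.

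**The concern.** The sentence that names the comparison also assigns its comparator away. Fluoxetine alone continues only for control participants who responded well, whereas the comparison is meant for those who responded poorly. If a difference appeared between the arms' poor responders in weeks 9-24, in either direction, it could be taken as evidence about early Shuganjieyu against fluoxetine alone. It would in fact mix four things: earlier versus later Shuganjieyu, a fluoxetine dose change made first in one arm only, differently selected patients, and rating-scale outcomes collected with treatment known. What is at stake is what the trial may conclude about its second period.

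**Working it through.** **1. The plan's own figure.** Inputs from the sample size section: difference 2.3, SD 4.3, two-sided alpha 0.05, power 85%, dropout 20%.

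n per group = 2 × (1.960 + 1.036)² × 4.3² / 2.3² = 62.8, so 63; 63 / 0.8 = 78.75, so 79. The t-test version gives 63.7, so 64, and 64 / 0.8 = 80. The stated 80 per group is reproduced. It is sized for the week-8 comparison in all randomised participants, and nothing below alters it.

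**2. The treatment rules side by side (Study design and Dosage Regimen).**

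| Week-8 HAMD-17 reduction | Experimental arm, weeks 9-24 | Control arm, weeks 9-24 |
|---|---|---|
| Under 50% | Shuganjieyu continues; fluoxetine dose changed | Shuganjieyu added first; fluoxetine change considered later |
| Over 50% | Combination continues | Fluoxetine alone |

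The stated purpose needs fluoxetine alone in the control cell of the under-50% row. It stands only in the over-50% row. Within the under-50% row the first drug changed also differs by arm, so a contrast there cannot separate the timing of Shuganjieyu from the fluoxetine change. Study design leaves a reduction of exactly 50% unassigned.

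**3. Selection into the subset (illustration).** The article gives no mean baseline HAMD-17. Assume one common baseline b for all participants, normally distributed change with SD 4.3, and the planned mean changes of -11 (control) and -13.3 (experimental). A reduction under 50% means a change greater than -b/2, so

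P(under 50%) = 1 - Φ((-b/2 - mean change) / 4.3).

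At b = 20: control 1 - Φ(1.0 / 4.3) = 0.408; experimental 1 - Φ(3.3 / 4.3) = 0.221.

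| Assumed baseline | Control | Experimental | Ratio |
|---|---|---|---|
| 20 | 41% | 22% | 1.8 |
| 22 | 50% | 30% | 1.7 |
| 24 | 59% | 38% | 1.6 |
| 26 | 68% | 47% | 1.4 |
| 28 | 76% | 57% | 1.3 |

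If the trial's own effect assumption holds, the two poor-response subsets differ in size at every assumed baseline. They are therefore selected differently by arm, and randomisation no longer makes them comparable.

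**The case against.** The strongest reply is that this is a loosely worded rationale for a period the article itself calls observational. The primary analysis is at week 8, is randomised and blinded, and is the one the trial is sized for. That stands in full.

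A reader might infer that the trial's aims also promise a long-term conclusion about poor responders. They do not. The Abstract says "it seeks to explore the long-term efficacy (in terms of improving residual symptoms and preventing relapse) and safety of this combination therapy", and the Introduction and Discussion likewise speak of exploring or assessing long-term efficacy, without naming poor responders. Nor is a week-24 poor-responder contrast a listed endpoint: the endpoints specific to the extension are relapse among those who had done well at week 8 and the rate of medication changes or additions. The problem is confined to the purpose stated in Study design.

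Two other readings deserve a hearing. Poor early efficacy could mean the participants with under 20% reduction at week 2, whose control members do stay on fluoxetine plus simulant, blinded, to week 8. But Study design ties the purpose to the week-8 50% rule, and the week-2 group is also formed after randomisation. Alternatively, early combination could mean combination from the start against delayed addition. The design can support that comparison, but it is not one against fluoxetine alone.

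Finally, the words may contain in Study design, and the description under Extended Study Period, leave room for some control poor responders to stay unchanged. Controls left unchanged at an investigator's discretion are not a planned comparator. The room for it is a conflict between sections that needs resolving.

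Detailed model specification belongs to the SAP, which is not shown, and its absence is not criticised. A SAP cannot, however, restore a comparator that the treatment rule removes.

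**Conclusion.** The concern holds for the purpose stated for the two-period design, and only for that. After week 8 there is no planned fluoxetine-alone comparator among poor responders, the arms change different drugs, the subset depends on a post-randomisation outcome, and follow-up is open-label. This conclusion rests on the treatment rules and on no numerical assumption.

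The percentages (41-76% of control and 22-57% of experimental participants under 50% reduction, for baselines of 20 to 28) depend on an assumed common baseline and on normality. A reader might infer a firm figure, such as half the control arm starting Shuganjieyu; the article does not support a single value. Nor does the point weaken the week-8 result: combination versus fluoxetine plus simulant in all randomised participants remains a valid blinded comparison.

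**What to change.** 1. Reconcile Study design, Extended Study Period and Dosage Regimen on what happens to control participants after week 8, including a reduction of exactly 50%. No clinical rule is proposed here.
2. Restate the purpose as a comparison of two randomised strategies: combination from the start, versus fluoxetine first with Shuganjieyu added for insufficient response, each with the week-8 adjustments that the reconciled text sets out. The fluoxetine change is then part of a strategy, and a difference is credited to the strategy as a whole.
3. Analyse HAMD-17 to week 24 in all randomised participants by original assignment, labelled exploratory and open-label.
4. Report the under-50% subset descriptively only, and state that combination versus fluoxetine alone is estimated only up to week 8.

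The cost is small. HAMD-17 is already scheduled at weeks 12, 16 and 24, so the change is one of wording plus one additional model. Participants who do not enter the extension will have missing later scores, which that model must handle. The long-term claim becomes more modest.

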**Figure 1 FIG1:**
[figure not shown]
Flowchart of the study HAMD-17: 17-item Hamilton Rating Scale for Depression

Basic Study Period (Weeks 0-8)

A multicentre, randomized, double-blind, placebo-controlled parallel design will be employed. During the basic study period, a stratified and block randomization method will be used. All participants will be randomly assigned at a 1:1 ratio to either the experimental group (Shuganjieyu capsules combined with fluoxetine) or the control group (Shuganjieyu capsule simulant combined with fluoxetine). The evaluation during the basic study period will be conducted via double-blind and single-simulation techniques; i.e., both the investigator and the participants will be required to remain “blinded” during the grouping and evaluation. Additionally, the preparation of the placebo used in the control group will ensure that it matches the experimental drug in sensory aspects (such as dosage form, shape, colour, texture, and odour). The placebo will not contain the active ingredients of the experimental drug. This design will minimize subjective errors and ensure the objectivity and reliability of the trial results.

Extended Study Period (Weeks 9-24)

A multicentre, open-label observational study will be conducted. After completing the 8-week treatment period in the basic study period, the investigator will adjust the dosing regimen according to the condition of the participants, either to continue maintaining the treatment regimen of the basic study period in the experimental/control group or to adjust the dosing regimen for the experimental group. The design of the extended study period aims to align with clinical practice.

Sample Size Calculation and Randomization and Blinding Methods

This study will be a superiority trial randomized 1:1 to the experimental group (Shuganjieyu capsules combined with fluoxetine) and the control group (Shuganjieyu capsule simulant combined with fluoxetine). The sample size will be calculated based on the following assumptions: the relative baseline change in the HAMD-17 score at 8 weeks is expected to be -13.3 for Shuganjieyu capsules combined with fluoxetine and -11 for the Shuganjieyu capsule simulant combined with fluoxetine. The difference in score reduction (δ) will be -2.3, the standard deviation (SD) will be 4.3, the two-sided type I error will be set at 0.05, and the statistical power will be 85%. Given a 20% dropout rate, each group will require 80 participants, resulting in a total of 160 participants.

In the basic study period of this trial, a stratified block randomization method will be adopted, with the study center as the stratification factor. Block randomization will be conducted within each center. The randomization list will be generated by the randomization statistician using SAS 9.4 statistical software (SAS Institute, Cary, USA) based on stratification factors and grouping ratios. Confidential parameters, including the number of blocks, block length, and random seed values, will be sealed in opaque envelopes along with the randomization list as the allocation schedule, which remains unopened during the trial. After completing the 8-week basic study period observation, investigators at each center will unblind the drug coding for individual patients.

Participant Selection

These criteria will standardize the study process, ensure its rigor, and protect the rights and interests of participants from an ethical perspective. The inclusion criteria for participants in this study will include the following: (1) meeting the diagnostic criteria for depression according to the Diagnostic and Statistical Manual of Mental Disorders (5th edition) (DSM-5); (2) aged 18-65 years (inclusive), regardless of sex; (3) HAMD-17 score ≥ 18 in the screening period, and Item 13 score ≥ 2; (4) negative pregnancy test; and (5) voluntary signing of the informed consent form and agreement to participate in all visits, examinations, and treatments according to the trial protocol. The exclusion criteria will include the following: (1) treatment-resistant depression (lack of clinical efficacy after adequate treatment with two or more different mechanisms of antidepressant drugs), depression caused by psychotropic drugs, depressive secondary to other mental illnesses, or somatic diseases at an active stage; (2) individuals meeting DSM-5 criteria for other mental disorders (such as schizophrenia spectrum and other psychotic disorders, bipolar and related disorders, anxiety disorders, obsessive-compulsive and related disorders, somatic symptoms and related disorders); (3) severe suicidal tendencies (HAMD-17 suicide score ≥ 3) or a tendency to harm others; (4) severe or unstable cardiovascular, cerebrovascular, liver, kidney, endocrine, digestive and blood diseases; liver function tests showing alanine aminotransferase (ALT), aspartate aminotransferase (AST) > 2 times the upper reference limit, or serum creatinine (SCr) > upper reference limit; patients with a history of hyperthyroidism, hypothyroidism, or other endocrine diseases currently in an active period; (5) patients who have undergone psychiatric surgery or electroconvulsive therapy in the past 3 months; those who have not responded to previous treatment with Shuganjieyu capsules or fluoxetine; those who have received or are currently receiving any other investigational drug therapy within 3 months before the trial; patients taking interfering drugs contraindicated with the investigational drug, or those who have received systemic antidepressant therapy within 4 weeks; patients with psychoactive substance abuse or dependence in the past 12 months; (6) patients with known or suspected allergies to *Hypericum perforatum*, *Eleutherococcus senticosus*, or fluoxetine; long-term use of caffeine and nicotine; and (7) other individuals who are deemed unsuitable for participation in this clinical trial by the researchers.

Participant treatment

Investigational Product

An overview of the schedule of assessments is shown in Table 1. During the basic study period (0-8 weeks), both the investigational drug Shuganjieyu capsules (0.36 g/capsule) and the placebo (simulant Shuganjieyu capsules) will be provided by Sichuan Jishengtang Pharmaceutical Co., Ltd. The basic drug fluoxetine (20 mg/capsule) is a commercially available drug that has undergone consistent evaluation.

**Table 1 TAB1:** Assessment schedule *Laboratory examination: Routine blood tests, routine urine tests, liver function tests, and renal function tests HAMD-17, 17-item Hamilton Depression Rating Scale; HAMA, Hamilton Anxiety Rating Scale; CGI, Clinical Global Impression; PHQ-15, Patient Health Questionnaire-15; PSQI, Pittsburgh Sleep Quality Index; DARS, Dimensional Anhedonia Rating Scale; TEPS, Temporal Experience of Pleasure Scale; Q-LES-Q-SF, Quality of Life Enjoyment and Satisfaction Questionnaire-Short Form.

Phase	Basic study period				Extended study period		
Visit Items	Visit 1	Visit 2	Visit 3	Visit 4	Visit 5	Visit 6 (Telephone follow-up)	Visit 7
Visit time	-3 to 0 day (Screening)	2 weeks ±3 days	4 weeks ±3 days	8 weeks ±3 days	12 weeks ±3 days	16 weeks ±3 days	24 weeks ±3 days
Sign informed consent form	●						
Demographic information	●						
Inclusion and exclusion criteria	●						
Vital signs	●	●	●	●	●		●
Physical exam	●	●	●	●	●		●
Laboratory examination *	●			●			●
Electrocardiogram	●			●			●
HAMD-17	●	●	●	●	●	●	●
HAMA	●	●	●	●	●	●	●
CGI	●	●	●	●	●	●	●
PHQ-15	●	●	●	●	●	●	●
PSQI	●	●	●	●	●	●	●
DARS	●	●	●	●	●	●	●
TEPS	●	●	●	●	●	●	●
Q-LES-Q-SF	●			●			●
Drug administration plan	●	●	●	●	●	●	●
Concomitant medication	●	●	●	●	●	●	●
Adverse events	●	●	●	●	●	●	●

Before dispensing investigational drugs (Shuganjieyu capsules/placebo) to participants, they must be packed identically and without any distinguishing marks. The blinded investigational drugs for the basic study period, which have passed quality inspection, will be delivered to each clinical trial centre. Drug administrators designated by each centre will manage and distribute the drugs uniformly, maintaining relevant records. This process ensures compliance with the double-blind trial design requirements.

Dosage Regimen

During the basic study, the experimental group will receive oral fluoxetine (20 mg/dose, once daily) with Shuganjieyu capsules (two capsules/dose, twice daily, morning and evening). The control group will receive fluoxetine (20 mg/dose, once daily) with Shuganjieyu capsule simulant (two capsules/dose, twice daily, morning and evening). If the HAMD-17 total score reduction rate is less than 20% at the end of the second week, the dosage of Shuganjieyu capsule or simulant will be adjusted to four capsules/dose, twice daily, in the morning and in the evening.

After completing the 8-week basic study period and entering case report form (CRF) data, the investigators at each centre will unblind the drug codes corresponding to individual participants. On the basis of the participants’ condition after 8 weeks of the basic study period, an extended study period medication plan was formulated. For participants who enter the extended study period, if their HAMD-17 total score reduction rate is less than 50%, the fluoxetine dosage will be adjusted to 40 mg/dose once daily for the experimental group. For the control group, Shuganjieyu capsules (two capsules/dose, twice daily, morning and evening) will be added first, and further adjustments to the fluoxetine dosage (40 mg/dose, once daily) will be considered on the basis of changes in the participant’s condition. Participants will be prohibited from concurrently using other antidepressant medications during both the basic and extended study periods. During the basic study period, the use of other auxiliary treatments for depression will be prohibited, such as psychotherapeutic intervention and rehabilitation therapy, modified electroconvulsive therapy, transcranial magnetic stimulation, vagus nerve stimulation, deep brain stimulation, and other physical therapies. During the extended study period, the use of other auxiliary treatments for depression will be prohibited, including modified electroconvulsive therapy, transcranial magnetic stimulation, vagus nerve stimulation, and deep brain stimulation, but psychological interventions will be permitted.

Each clinical trial centre will perform unblinding only for participants who meet the specified criteria. Participants who do not complete the 8-week visit during the basic study period will remain blinded. Once all participants’ 24-week CRF data are fully entered and after any queries are addressed and no outstanding issues are observed, the data will be locked for final analysis.

Efficacy and safety indicators

Efficacy Indicators

The efficacy assessment indicators will include the following: (1) the primary efficacy endpoint will be the change in the HAMD-17; (2) the secondary efficacy endpoint will include the change in the Hamilton Anxiety Rating Scale (HAMA), Clinical Global Impression (CGI), Patient Health Questionnaire-15 (PHQ-15), Pittsburgh Sleep Quality Index (PSQI), Dimensional Anhedonia Rating Scale (DARS), Temporal Experience of Pleasure Scale (TEPS), and Quality of Life Enjoyment and Satisfaction Questionnaire-Short Form (Q-LES-Q-SF); the rate of patients with dose adjustments during the basic study period (8 weeks); the rate of relapse of depression symptoms at 12, 16, and 24 weeks of treatment in subjects who achieve clinical recovery/remission at 8 weeks of treatment; and the rate of medication changes/additions in participants who complete 8 weeks of treatment and enter the extended study period.

In this context, relapse will be defined as the recurrence of symptoms after achieving partial relief (effective, HAMD-17 reduction rate ≥ 50%) or clinical remission (complete symptom disappearance, HAMD-17 score ≤ 7) after the acute period of treatment [21].

Safety Indicators

The safety evaluation indicators will include the following: (1) vital signs: temperature, pulse, respiratory, and blood pressure; (2) routine blood parameters: red blood cell (RBC), haemoglobin (Hb), white blood cell (WBC), neutrophil percentage (NEUT%), and platelet (PLT); (3) routine urine parameters: urine protein (PRO), urine glucose (GLU), urine occult blood (BLD), and urine leucocyte (LEU); (4) liver function indicators: alanine aminotransferase (ALT), aspartate aminotransferase (AST), alkaline phosphatase (ALP), total bilirubin (TBIL), and gamma-glutamyl transferase (GGT); (5) renal function indicators: blood urea nitrogen (BUN), serum creatinine (Scr), uric acid (UA), and estimated glomerular filtration rate (e-GFR); (6) electrocardiogram examination: standard 12-lead electrocardiogram; and (7) adverse events: all adverse events occurring during the whole trial will be recorded at any time. The subsequent safety analysis includes an analysis of the potential correlation between adverse events and the investigational drugs. When adverse events occur, the safety of the subjects will be given first priority. Depending on the nature and severity of the adverse events, different treatments will be implemented, such as termination of the clinical trial, adjustment of drug dosage, and symptomatic treatment.

Quality control

This study was approved by the Ethics Committee of Peking University Sixth Hospital (approval NO. 2022-3) and registered at Clinicaltrials.gov (identification number: NCT05361330; Registered 4 May 2022, https://clinicaltrials.gov/study/NCT05361330). Investigators and their affiliated medical institutions will be required to follow the protocol approved by the Ethics Committee and the Clinical Trials Act during clinical trials to ensure the legality and compliance of the trial process. Additionally, during the course of the project, any deviations from the approved trial protocol will be thoroughly documented, explained, and properly archived by the trial institution and the project undertaker.

Given that this study is a multicentre clinical trial, the primary efficacy assessment will be based on scale evaluations. To ensure consistency in scale assessments across multiple centres, systematic training on the study protocol and scales will be conducted before project initiation. Standard operating procedures (SOPs) will be established on the basis of relevant study procedures and patient management.

In addition, to ensure the accuracy and reliability of the trial data, all the clinical examination laboratories of the medical institutions involved in the clinical trials will establish high-standard quality management and operation. For non-laboratory indicators, such as physical examinations, temperature measurements, and blood pressure measurements, each research unit will select recognized and quality-controlled measurement methods and instruments to ensure consistency when conducting examinations across different centres and personnel.

The project will have clinical research associates who have received professional training, with adequate scientific and clinical knowledge, as well as the required qualifications. Moreover, the project team will formulate a detailed monitoring plan and SOP to ensure the unified monitoring process and standards of clinical research associates. After the trial started, clinical research associates will conduct regular onsite monitoring visits and keep relevant records at the trial institution to ensure the accuracy and completeness of the trial records and reports. Moreover, they will actively monitor and check the implementation of the clinical trial protocol to ensure that the trial strictly follows relevant norms and regulations, guaranteeing its accordance with scientific principles, research rigor, and compliance.

Data collection and management

Data Collection

This study will focus primarily on scale assessments, with data collection to include demographic information, mood scales, somatic symptom scales, and quality of life scales.

Demographic information: Demographic information will be collected from the demographic characteristics (e.g., age, sex), baseline data, and previous treatments of the participants in each group to evaluate the baseline balance between the two groups.

Mood indicators: The HAMD-17, HAMA, TEPS, and DARS will be used to assess the participants’ depression, anxiety, and daily experiences of pleasure. These scales will provide a comprehensive understanding of various aspects, from emotional states to physiological symptoms.

Somatic symptom indicators: The PHQ-15 and PSQI will be used to assess the participants’ symptoms of somatic discomfort and sleep quality. These two scales will provide validated measures for the medical field and help provide a comprehensive understanding of patients’ somatic symptoms and sleep status.

